#### **Correlative translational research:**

- (1) Germline Biomarkers: the discovery of microRNAs (miRNAs) has led to an enormous advance in our understanding of human genetics. As their function and biology has been uncovered, it has become clear that miRNAs and their binding sites in the 3' untranslated region (3'UTR) of genes explains much of the mystery about the importance of inherited variability of non-coding regions of the genome. Through significant understanding of miRNAs, new germ-line genetic markers of cancer risk as well as predictive biomarkers of response to cancer therapy have rapidly emerged(10, 11). To collect germline information, whole blood or buccal swabs will be collected at baseline, during or after treatment.
- (2) Immune profiling: Soft tissue sarcomas are known in some cases to respond to immune-based therapies (12, 13). These tumors are known to have a dense infiltrate of macrophages, which can have tumor-promoting characteristics. The presence of macrophages within the tumor microenvironment is known to be associated with worse prognosis across several malignancies(14). Likewise, radiotherapy (in particular hypofractionated radiotherapy), can result in the recruitment of macrophages to the tumor microenvironment, which can promote resistance to radiotherapy(15). Approaches that modulate macrophage infiltration and function are gaining clinical interest. To understand the impact of macrophages on prognosis and treatment response, and define potential therapeutic of targeting macrophages in soft tissue sarcomas, especially in

combination with hypofractionated radiotherapy, we plan to evaluate formalin-fixed paraffin-embedded tissue from pre-treatment biopsy for patients where this tissue is available. We will collect post-radiotherapy surgical specimens at the time of surgery, which will be used fresh, frozen, or formalin-fixed and paraffin-embedded for subsequent use. We will also collect ~10-20 mL whole blood in tubes containing anticoagulant (e.g. EDTA) prior to radiotherapy, during radiotherapy, after radiotherapy and after surgery, to evaluate dynamic changes in peripheral immune system to evaluate the impact of radiotherapy and surgical removal of the disease. Whole blood will be analyzed immediately by flow cytometry, and plasma and PBMC will be frozen for future analysis.

T cell based immunotherapies are an emerging therapy in the treatment of many malignancies, and there is interest in soft tissue sarcoma. This therapy may be predicated on the presence of nonsynonymous mutations within the tumor that are recognized by the immune system (neoepitopes), and the presence of functional T cells within the tumor microenvironment. New computational methods may allow for prediction of neoepitopes using next-generation sequencing of the tumor(16). Next-generation sequencing (NGS) of sarcomas has led to deeper understanding of disease categorization and subtype and revealed potential therapeutic targets(17). Tumor-specific T cells can be evaluated using deep sequencing of T cells isolated from the tumor. However, despite these tools, implications of sarcoma genomics on the anti-tumor immune response are not understood. To this aim, we will collect tumor specimens at the time of surgery for the isolation of immune cells from the tumor and for next generation sequencing of the tumor.

- (3) Distant metastasis after local therapy for soft tissue sarcoma continues to be a clinical obstacle. Comparing the genomic landscape of primary and metastatic lesions may provide insight into the timeline of evolution of metastasis in sarcoma, and inform better adjuvant therapies. Thus, for patients who undergo surgery for relapsed or metastatic sites, we will also collect tumor specimens at the time of surgery to isolation of immune cells from the tumor and for next generation sequencing.

## **6.0 PHARMACEUTICAL INFORMATION**

### **6.1 Investigational Agent or Device**

Not applicable.

### **6.2 Availability**

Not applicable.

### **6.3 Agent Ordering**

Not applicable.

### **6.4 Agent Accountability**

Not applicable.

## **7.0 ADVERSE EVENTS: LIST AND REPORTING REQUIREMENTS**

Toxicity assessment will be performed using the National Cancer Institute Common Terminology Criteria for Adverse Events (NCI-CTCAE) Version 4.0 for early ( $\leq 3$  months), and late ( $> 3$  months) radiation toxicity. Dose limiting toxicity will be defined as any treatment-related grade 3 or higher toxicity in the following categories: skin and extremity. In addition, any other grade 4 or 5 toxicity attributed to the therapy will be reported immediately.

### **7.1 Treatment Toxicities**

#### **7.1.1 Constitutional symptoms**

Constitutional symptoms that may be attributed to radiation therapy include fatigue, loss of appetite, nausea and vomiting. Patients will be seen on a weekly basis while they are receiving radiation therapy, per standard of care. Counseling and medications may be prescribed to alleviate these symptoms while the patient is on treatment. It is expected that symptoms will improve and resolve 2-4 weeks after completion of therapy.

#### **7.1.2 Radiation-induced skin toxicity**

Patients may develop acute skin toxicities which will be monitored during and after their treatment. Wound complications that occur as a result of skin toxicities will be monitored within 3 months after surgery and scored as a major wound complication per the criteria set forth in Appendix.

## 8.0 STUDY CALENDAR

|                                                                        | Pre-Treatment                    |        | Treatment      |                                      | Follow-up                                        |                                                                   | Relapse/Metastatic Site (if applicable) |
|------------------------------------------------------------------------|----------------------------------|--------|----------------|--------------------------------------|--------------------------------------------------|-------------------------------------------------------------------|-----------------------------------------|
|                                                                        | Pre-Study                        | Pre-RT | RT             | Surgery within 12 wks post radiation | Within 3 months from time of surgery(+/- 1 month | Every 6 months, up to 5 years (+/- 2 months) from time of surgery |                                         |
| History & Physical                                                     | X                                |        |                |                                      | x                                                | x                                                                 |                                         |
| Consent                                                                | X                                |        |                |                                      |                                                  |                                                                   |                                         |
| CT Chest                                                               | X                                |        |                |                                      |                                                  | X (every 6 months x 3 years) (+/- 2 months)                       |                                         |
| CT or MRI of primary site                                              | X                                |        |                |                                      |                                                  | X (every 6 months x 3 years) (+/- 2 months)                       |                                         |
| Pregnancy test                                                         | X                                |        |                |                                      |                                                  |                                                                   |                                         |
| Tissue collection                                                      |                                  |        |                | x                                    |                                                  |                                                                   | X                                       |
| Blood Collection                                                       |                                  | X      | X  | X*                                   | X*                                               | X                                                     | X                                       |
| MRI/CT Simulation and RT Planning                                      |                                  | X      |                |                                      |                                                  |                                                                   |                                         |
| Radiotherapy                                                           |                                  |        | X              |                                      |                                                  |                                                                   |                                         |
| Surgery                                                                |                                  |        |                | X                                    |                                                  |                                                                   |                                         |
| Clinical Follow-up                                         |                                  |        |                |                                      | X                                                | X                                                                 |                                         |
| Wound Assessment/Complication
RTOG/EORTC
TESS
MSTS
CTCAEv4 | X 
X  |        |                |                                      | X 
X

X                     | X
X 
X 
X                        |                                         |

 Serum study draw will occur whenever feasible, approximately Midpoint of radiation treatment (+/- 2 weeks), or at the discretion of the Investigator.

 Serum samples will be drawn whenever feasible, approximately at 6 month follow-up visits, (+/- 2 months), or at the discretion of the Investigator.

Wound complications will be assessed for the first 120 days after the completion of surgery

 TESS questionnaires will be completed by the patient at baseline, approximately 12 months, 18 months and 24 months from the start of treatment. These may be administered electronically or via telemedicine.

 MSTS will be completed by the PI at baseline, approximately 12 months, 18 months and 24 months from the start of treatment

 Whenever feasible and in the best interest of the subject, follow-up visit may occur via telemedicine.

\*annotates optional

---

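### Calendar footnote 1 names serum for the only on-treatment blood draw, whereas the immune profiling section requires anticoagulated whole blood at that point

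*Protocol*

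**What the plan says.** Two parts of the Protocol describe the research blood draws.

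The correlative translational research section, item (2) Immune profiling, gives the specimen, tube, approximate volume and occasions. About 10 to 20 mL is to be taken as "whole blood in tubes containing anticoagulant (e.g. EDTA) prior to radiotherapy, during radiotherapy, after radiotherapy and after surgery". It then gives the processing: "Whole blood will be analyzed immediately by flow cytometry, and plasma and PBMC will be frozen for future analysis".

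The study calendar in section 8.0 has one row, "Blood Collection", whose label gives no specimen type. Two of its marks carry numbered footnotes. Footnote 1, on the radiotherapy column, reads "Serum study draw will occur whenever feasible, approximately Midpoint of radiation treatment", with 2 weeks' leeway either side or as the investigator decides. Footnote 2, on the 6-monthly follow-up column, reads "Serum samples will be drawn whenever feasible, approximately at 6 month follow-up visits, (+/- 2 months), or at the discretion of the Investigator". The marks at surgery and at the visit within 3 months of surgery are flagged as optional. The pre-radiotherapy and relapse marks have no footnote.

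The samples feed item 3.3 of the Statistical Methods in the Synopsis. That item is an exploratory evaluation of how radiation affects local and systemic immune responses, based on tumor and blood specimens.

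**The concern.** Serum is the fluid left after blood has clotted. It has no cells for flow cytometry or for PBMC, and it is not plasma. A mid-radiation draw taken and processed as footnote 1 describes would supply none of the three materials that the immune profiling section asks for. Because flow cytometry is to be done at once on fresh blood, a wrong tube cannot be put right later.

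The stated aim is to follow dynamic change in the peripheral immune system. That needs one specimen type across occasions within a patient, and the mid-radiation draw is the only one taken during treatment. Accrual to the expansion cohort is expected to take up to 7 years, toward 205 patients, so an ambiguity in the draw instruction could persist for a long time before anyone noticed it.

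**Working it through.** There is no sample size, rate or error level to recompute. The check is a comparison of the two sections and a count of the calendar marks.

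**Step 1: specimen by occasion.**

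| Calendar column | Mark | Specimen named in the calendar | Matching occasion in the immune profiling text |
|---|---|---|---|
| Pre-RT | required | none | before radiation: anticoagulated whole blood |
| RT | footnote 1 | serum | during radiation: anticoagulated whole blood |
| Surgery | optional | none | could serve as after radiation |
| Within 3 months of surgery | optional | none | could serve as after surgery |
| Every 6 months, up to 5 years | footnote 2 | serum | not listed; could be read as after surgery |
| Relapse or metastatic site | required | none | no blood occasion listed |

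**Step 2: counts.** Six columns are marked and 2 carry a serum footnote (2/6). Leaving out relapse gives 2/5. Leaving out the two optional draws as well gives 2/3. On treatment there is one draw, and it is labelled serum (1/1).

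**Step 3: is serum wanted for something else?** Apart from these footnotes, serum appears in the Protocol only as an option for the pregnancy test (Synopsis eligibility, sections 3.1.6 and 4.2). The germline work uses whole blood or buccal swabs. No serum assay is described, so the footnotes name a material for which the Protocol states no use.

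**Step 4: where the conflict is direct.** For the mid-radiation draw, both sections address the same occasion and name different specimens, so the contradiction needs no interpretation. For the 6-monthly draws it depends on how they are read. The immune profiling text lists four occasions and does not mention 6-monthly sampling. Its post-surgery sample could be the optional 3-month draw, which has no serum wording. Footnote 2 conflicts only if the 6-monthly draws are meant to be those post-surgery samples.

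**Step 5: consequence under each reading.**

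- Immune profiling text followed: the right tube is drawn and nothing is lost.
- Footnotes followed: the on-treatment sample has no cells and no plasma. Any cellular comparison then rests on the pre-radiotherapy draw against the surgery and 3-month draws, and both of those are optional. In a patient who skips both, the pre-radiotherapy draw is the only one before relapse not labelled serum, so no cellular change can be measured before relapse.

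**The case against.** The strongest reply is that the immune profiling section is the only place that specifies tube, volume and processing, and it specifies them correctly for the on-treatment draw. The footnotes mainly set timing and feasibility, and serum may simply be loose usage for blood. A team working from the immune profiling text collects the right specimen. This stands. A reader might infer that the samples as planned cannot yield the measurement, or that none of the footnoted draws could support flow cytometry. The document does not support that: both statements hold only if the footnotes are followed in preference to the other section, and the Protocol does not say which governs.

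A reader might also infer that anticoagulated whole blood is required at every calendar time point. It is not, because the immune profiling text names four occasions only. Nor does the Protocol plan any comparison of plasma with serum, so a specimen effect confounded with the radiation effect is a conjecture. The serum could be an additional tube.

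Finally, the stakes are modest. Item 3.3 is exploratory, the listed exploratory objectives name germline work and tissue but not blood immune profiling, and the two footnoted draws are already subject to feasibility and investigator discretion. That limits the weight of the point. It does not remove the contradiction, because footnote 1 is an operative instruction and it names the wrong material for the only planned use.

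**Conclusion.** The Protocol contradicts itself on the specimen for the mid-radiation draw. For the 6-monthly draws there is a conflict only if they are meant as the post-surgery samples of the immune series. The size is 2 of 6 marked blood columns worded as serum, including the sole on-treatment draw. The possible loss is the on-treatment point of one exploratory analysis, patient by patient, wherever the footnote is followed. How often that would happen cannot be estimated from the document.

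The conclusion assumes that serum carries its ordinary meaning and that no separate document assigns the serum a purpose. Primary and secondary endpoints are untouched. This is an inconsistency to correct, not a design that makes the measurement impossible.

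**What to change.** In footnote 1, replace the words *Serum study draw* with: *whole blood in anticoagulant (e.g. EDTA) tubes, as in the immune profiling section*.

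In footnote 2, decide whether the 6-monthly draws belong to the immune series. If they do, name the same specimen there and add the 6-monthly visits to the occasions listed under immune profiling. If they do not, state what the serum is for.

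The on-treatment correction adds no draw and asks for nothing beyond what the immune profiling section already specifies. The cost is the wording of two footnotes and, if the 6-monthly draws join the series, one line in the immune profiling text plus processing of those samples in the same way.

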## **9.0 DATA REPORTING/REGULATORY CONSIDERATIONS**

### **9.1 Monitoring Plan**

The JCCC DSMB meets monthly to review all SAE reports for trials overseen by the JCCC DSMB. All SAE reports, which have been filed since the previous meeting, are presented to the committee for review.

For trials overseen by the JCCC DSMB, the DSMB reviews all dose-limiting toxicities (DLTs) for dose-escalation studies. Protocol suspensions and re-opening of accrual to the next cohort based on DLT evaluation fall under the purview of the DSMB.

For all JCCC oncology trials and TRIO-US studies where the JCCC DSMB has primary oversight, all SAEs shall be reported to the JCCC DSMB in a timely manner [ten days, two days for a death] regardless of relationship and expectedness. The JCCC ORC will review all submissions and the ORC staff will enter the information into the JCCC Clinical Trials database. Reports are generated for full JCCC DSMB review. For trials where the JCCC DSMB has primary DSMB review responsibility, the DSMB requires that the PI generate cumulative adverse event reports for quarterly, biannual or annual review.

The DSMB reviews each SAE report and determines whether or not protocol modifications are warranted to ensure subject safety. In this review, prior occurrences of similar toxicity with the therapy under study are taken into consideration, as well as the severity of the event and the likelihood that it was related to a study drug. The DSMB may recommend no changes to the study if the event is expected or related to other causes such as the subject's underlying condition. The DSMB may request an expert's advice of another non-Principal Investigator with national experience to support their deliberations and decisions.

The JCCC DSMB has the authority to recommend to the UCLA IRB the immediate halt to a study (i.e., discontinuation of any further treatment of enrolled subjects and discontinuation of enrollment of new subjects) should there be any serious unexpected toxicity that warrants further investigation.

Requests for single subject exceptions/waivers from the approved study protocol, including out of window procedures and eligibility deviations, must be reviewed and approved by a member of the DSMB. Each trial is assigned a primary and secondary reviewer who is responsible for reviewing each exception/waiver request for that trial. Approvals and disapprovals of the request are sent to the Principal Investigator via email and copied to the UCLA IRB. Requests for single subject exceptions/waivers are made

by the Principal Investigator via email utilizing the “Single Subject Exception Request Form.”

JCCC DSMB correspondences are addressed to the Principal Investigator and copied to the UCLA IRB. Minutes of the DSMB meetings are maintained in a computer file.

**Confidentiality:** Each member of the JCCC DSMB is responsible for maintaining strict confidentiality of the study data. Members will not share any study data or information about the study with any individual external to the JCCC DSMB or the statistical working group for the study. The DSMB members may contact the statistical working group directly with questions regarding the operational details associated with the data analysis and summary presentations. Communication of deliberations or recommendations of the JCCC DSMB, either written or oral, should not be made outside of the Committee or the statistical working group. Outcome results are strictly confidential and must not be divulged to any non-member of the JCCC DSMB except in those cases where DSMB is required to inform the UCLA IRB of its determinations. Disclosure of outcome results to the IRB must only occur with written approval of the DSMB. A member who believes he or she may have a potential intellectual or financial conflict of interest during the course of review of the data must inform the chairperson of the DSMB. In such case, the meeting minutes will record the disclosure of the potential conflict of interest and that the individual recuse himself from the discussions and abstains from voting on the DSMB decision.

The development of complications will be monitored. If rates of development of acute wound complications exceeds 50% of patients, the study will be terminated because it will be assumed that the regimen is toxic compared with standard pre-operative radiation therapy where wound complication rates are reported to be 43% based on the NCIC study.

### **Level of Risk of a Study**

All interventional clinical trials undergo scientific review by the Internal Scientific Peer Review Committee (ISPRC) which requires that a Data and Safety Monitoring Plan is in place before a trial can be approved to begin. For trials overseen by the JCCC DSMB, the JCCC DSMB will determine the degree of risk of the study and will ensure that there are procedures in place to ensure the safety of the subjects that are enrolled in the trial. The intensity level of study oversight is determined by the risk category. Some of the factors that are considered when assigning the Level of Risk category include:

- A biostatistical design and appropriate procedures for proper data management so that the information collected can be properly validated.
- Appropriate Serious Adverse Event reporting procedures must be in place.
- The study duration must be appropriate and must be based on a realistic rate of enrollment.

- 
- Data collection and data management must be adequate to verify and ensure subject eligibility.

